**Methods:**

*Design*: A mixed-methods design will be used, based upon the RE-AIM framework (see <http://www.re-aim.hnfe.vt.edu/>). Objective 1 (Reach) will refer to a pre-existing dataset from a random cross-sectional population-level household survey previously conducted by MSF for separate purposes; routine cohort data from two MSF clinics in Irbid; and qualitative data from focus groups, semi-structured and key informant interviews. Objective 2 (Effectiveness) will use a cohort study design of chronic disease patients at the MSF-run clinics in Irbid. It will use routine clinic data to explore trends in clinical outcomes and other quality of care indicators, which occurred during MSF’s implementation of this NCD care model in Irbid. It will also include descriptive analysis of total and unit programmatic costs. Objective 3 (Adoption/acceptance) will use qualitative data to explore issues around adoption and acceptance of the model components through participant observation, focus group discussions and semi-structured interviews with patients, staff and key stakeholders. A small exploratory study to develop and test a short survey of self-reported medication adherence and beliefs will also be undertaken. Objective 4 (Implementation) will use routine cohort data, clinical audit, participant observation, routine costing data and qualitative data (as described above). Objective 5 (Maintenance) uses routine cohort data, qualitative data (as described above) and data on medical supplies, costs and staff time estimates.

*Study participants:* The pre-existing cross-sectional health service access survey included Syrian refugees households living outside of camp settings in Irbid governorate, selected using a two-stage cluster design. For the routine cohort data, all patients six years and older with confirmed NCDs attending the two MSF clinics in Irbid more than once, will be included (using patient records from January 2015 to December 2016). For the qualitative research, respondents will be purposively selected patients and/or health workers, past and present, from the two MSF clinics in Irbid. Key stakeholder interviews will include staff from MSF and other NGOs, Jordanian MoH staff and community leaders. For the medication adherence survey, a random sample of 300 consenting service users attending the MSF clinic will be selected.

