| “Effectiveness”/ Quality of Care  What are the trends in clinical outcomes and quality indicators of the programme?  What are the perceived benefits/unintended consequences from a patient and provider perspective? | Clinical Outcomes | No./% patients with hypertension that have a most recent BP <= 140/90 6 and 12 months post enrolment and trend from baseline  Number / % of patients with diabetes that have a most recent BP <= 140/90 6 and 12 months post enrolment and trend from baseline  Number / % of patients with diabetes with last HbA1c < 8.0 %/ 7.0 % 6 and 12 months post enrolment and trend from baseline  Number/% with a reduction of >= 0.5 mmol/L in cholesterol level from baseline 6 and 12 months from enrolment  Number/% of patients with asthma / COPD free from exacerbations/ admissions in the previous 6 months  Number / % of patients who report decreased/quitting smoking within reporting period  Number / % of patients who report increased levels of exercise from baseline during reporting period  Trend recommended referrals to another facility for acute complications/specialist care, as a proportion of active cohort | Routine facility cohort data  Costing data (for incremental costing analysis)  2 Focus group with patients  Semi-structured interviews with approximately 12 clinic staff and 16 patients |
|  | Quality Indicators | Proportion of recommended referrals to other services that are appropriate as per guideline  Number/ % of active patients with CVD prescribed a statin during reporting period  Number/ % of patients with CVD prescribed aspirin during reporting period  Number/ % of patients with CVD prescribed at least one anti-hypertensive during reporting period  Number/% of patients with COPD/asthma with inhaler technique check documented  Number/ % of times when appropriate clinical action taken based on clinical or laboratory findings according to guideline (see Annexe 2d for detail)  Trend in defaulters as a proportion of active cohort during reporting period  Description of cohort deaths (patient characteristics) | Clinical audit  Participant observation  Routine health facility cohort data |
|  | Perceived Effectiveness | Patient and providers perspectives on effectiveness of programme components (clinical review, medications, HE, HLO, MHPSS, HV) | Key informant interviews  2 Focus groups with patients  Semi-structured interviews with 12 MSF/clinic staff and 16 patients |

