### 3.4.2 Cohort study main outcome measures

The principal **clinical outcome measures** for patients in the cohort are:

DM: HbA1c < 7 or 8%; proportion of patients meeting individualised target at last visit within the reporting period and trend from baseline

Hypertension: BP < 140/90 mmHg: proportion of patients at target at last visit within the reporting period and trend from baseline

Cardiovascular disease: change in total cholesterol level from baseline

Asthma / COPD: Free from exacerbations / admissions in last six months

The principal **quality of care outcome measures** are the following:

Number/ % of active patients with CVD prescribed a statin during reporting period

Number/ % of patients with CVD prescribed aspirin during reporting period

Number/ % of patients with CVD prescribed at least one anti-hypertensive during reporting period

Number/% of patients with COPD/asthma with inhaler technique check documented

Number/ % of times when appropriate clinical action taken based on clinical or laboratory findings according to guideline (see Annexe 2e for detail)

Description of trends and patient characteristics in programme defaulters and deaths

Proportion of recommended referrals to other services that are appropriate as per guideline

Death is defined as confirmed death reported by family or community member. A defaulter is defined as a patient who has not attended any NCD clinic appointments within the last 90 days, is not known to have died or moved out of the area, and has not been successfully contacted by phone on two occasions by the clinic registrar. The definition was changed in October 2016 to reflect the newly extended appointment interval for stable patients to: two consecutive missed appointments; not known to have died, moved out of the area, or become immobile and ineligible for home care; and has not been successfully contacted by phone on two occasions by the clinic registrar.

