### 3.4.3 Cohort data sources

The cohort will use retrospective routine facility data collected from files of patients admitted from the start of January 2015 to the end of December 2016. Data on costs for the economic analysis will be obtained from logistics supply, accounting and pharmacy records, and from time estimates obtained through observation and discussions with staff (see below for more details).

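### The defaulter definition changes in October 2016, inside the record window, so the last quarter or less of the planned default trend is not comparable with earlier months

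*Protocol*

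**What the plan says.** Section 3.4.2 of the protocol lists among the principal quality-of-care measures "Description of trends and patient characteristics in programme defaulters and deaths". Table 2 adds the indicator "Trend in defaulters as a proportion of active cohort during reporting period".

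Section 3.4.2 then gives two case definitions for this one outcome. Under the first, a defaulter is a patient who "has not attended any NCD clinic appointments within the last 90 days". The section continues: "The definition was changed in October 2016 to reflect the newly extended appointment interval for stable patients to: two consecutive missed appointments". With its exclusions, the new criterion is "two consecutive missed appointments; not known to have died, moved out of the area, or become immobile and ineligible for home care". Both versions also require two failed attempts at contact by phone.

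The Executive Summary says that the cohort is built "using patient records from January 2015 to December 2016". Section 3.4.3 describes "files of patients admitted from the start of January 2015 to the end of December 2016", which is an admission window with no stated end of follow-up.

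**The concern.** A trend is readable only if every point on it counts the same thing. Here the case definition changes within the series, and three features of the change act together:

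- The time from last attendance to being flagged is fixed at 90 days under the old rule. Under the new rule it depends on the patient's appointment interval.
- The protocol says the rule changed because appointment intervals were lengthened, so the visit schedule and the definition moved at about the same time.
- The added exclusion removes some patients from the numerator whatever their interval.

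No passage says that one rule covers the whole window, that both are run side by side, or that the series is split. The only adjustment for change over time, in section 3.4.5, compares patients by period of entry. It cannot help, because the rule changes by calendar date for patients of every entry period. Section 1.1.4 also reports closure to new patients from May to October 2016, so a late-2016 step could not be attributed to any one cause. The affected points are the most recent ones, and section 5.3 has cohort data shared with stakeholders to guide delivery of care.

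**Working it through.** The protocol gives no default rate, sample size or appointment interval for this measure, so there is no stated figure to reproduce.

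**Share of the window affected.** 1 January 2015 to 31 December 2016 is 365 + 366 = 731 days. The day of the switch in October is not given. From 1 October the new rule covers 31 + 30 + 31 = 92 days, and 92/731 = 12.6%. From 31 October it covers 1 + 30 + 31 = 62 days. This takes records to stop in December 2016.

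**Time to being flagged.** Old rule: 90 days after last attendance. New rule: about 2 × I for appointment interval I, when the second appointment in a row is missed.

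**Effect on the count with unchanged behaviour.** Assume constant silent drop-out, a switch on 1 October, interval I already in force, and the phone criterion and new exclusion left aside. Patients last seen more than 90 days before the switch were already flagged. In the 92 days after it, the new rule captures drop-outs from 90 days before the switch up to 92 − 2I days after it, which is 182 − 2I days' worth. The preceding 92 days captured 92 days' worth. The ratio is (182 − 2I)/92, and the drop-out rate cancels.

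| Assumed interval (days) | Flag day, new rule | Shift from 90 days | Ratio, last 92 days to previous 92 |
| --- | --- | --- | --- |
| 30 | 60 | −30 | 122/92 = 1.33 |
| 45 | 90 | 0 | 92/92 = 1.00 |
| 60 | 120 | +30 | 62/92 = 0.67 |
| 90 | 180 | +90 | 2/92 = 0.02 |

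An even mix of 30- and 90-day intervals gives (122 + 2)/2 = 62, and 62/92 = 0.67. The only related figure in the protocol is the one-month maximum between prescription renewals in section 1.1.2, so even the direction cannot be settled from the document.

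**Active denominators.** 'Active' is not defined. Section 1.1.6 lists default among the programme exits, so it is an inference that defaulters leave the active cohort. If they do, drop-outs not yet recognised make up about h × L/30.44 of truly active patients, for monthly drop-out h and lag L in days. With h assumed at 1 to 3%:

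- L = 60: 2.0 to 5.9%
- L = 90: 3.0 to 8.9%
- L = 180: 5.9 to 17.7%

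Moving from a 90-day lag changes the denominator by about 1 to 3 points down (60 days) or 3 to 9 points up (180 days), once the new lag has fully built up.

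**The case against.** The change is dated and explained in the outcome section, so nothing is hidden. It touches at most 3 of 24 months of one descriptive measure among seven quality measures. Sections 3.4 and 6 disclaim any inference about effectiveness. Harmonising a variable across a known definition change is often left to an analysis plan. This lowers the severity, but it does not remove the point: the protocol itself writes two incompatible definitions into one planned trend, and following it as written produces the artefact.

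The flag-day arithmetic omits the phone criterion, which is common to both rules and weakens the contrast by an unknown amount. The ratio of 0.02 also needs every patient to have been on 90-day appointments before the switch, although the protocol describes the interval as newly lengthened. Both points stand, so the ratios show a range and are not estimates.

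Three stronger readings are tempting and are not supported:

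- A reader might infer that every active-cohort indicator breaks. Of those using the term as a denominator, only referrals is a stated trend; statin prescribing and health education are proportions over a reporting period. The blood pressure, HbA1c, aspirin and anti-hypertensive indicators do not use the term.
- A reader might infer that a patient on 90-day appointments last seen after 4 July 2016 (31 December minus 180 days) could never be counted. That presumes the longer interval already applied in July, and that records stop on 31 December. It also ignores the old rule, which ran until some day in October: if the switch came on 31 October, anyone last seen by 2 August had already reached 90 days.
- A reader might infer that a fixed 90-day rule throughout is the natural repair. If the lengthened interval reaches about 90 days, that rule would count patients attending on schedule as defaulters.

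**Conclusion.** The concern holds for the default trend. Two case definitions are fixed for one principal quality measure, the switch falls inside the record window, and no bridge is stated. The last quarter or less of the series (62 to 92 of 731 days) cannot be compared with earlier months. This takes records to end in December 2016, as the Executive Summary suggests; later follow-up would lengthen the new-rule segment.

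The sign and size of the artefact are not known from the protocol. Under the assumed 30- to 90-day intervals it could run from a rise of a third to a near-total fall with no change in behaviour. For active denominators, chiefly the referral trend and to a lesser degree statin prescribing and health education, a shift of a few points is plausible but conditional on an undefined term. The point is should-fix, because no test or sample size depends on the measure.

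**What to change.** All of this concerns counting the outcome, not how the clinics follow patients up.

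1. For the trend, derive default for all patients over the whole window from recorded visit dates, with one fixed rule and the same exclusions throughout.
2. Set the no-attendance threshold longer than the longest scheduled appointment interval in use, for example 180 days if that exceeds it. Give the 90-day version as a sensitivity analysis.
3. Count no defaults after the last date on which the rule can be observed.
4. Show clinic-recorded status, which carries the phone criterion, as a separate series with the October 2016 break marked. Do not read a step there as programme performance.
5. Define 'active' consistently with the fixed rule.

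The cost is a short script on existing data and a paragraph of text. The derived rates will differ from those recorded by the clinics and will lack the phone criterion. There will also be fewer evaluable months at the end: if default is dated to last attendance and records stop on 31 December 2016, the last evaluable date is 4 July under a 180-day threshold (31 December minus 180 days) and 2 October under 90 days (31 December minus 90 days).

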### 3.4.3 Cohort data sources

The cohort will use retrospective routine facility data collected from files of patients admitted from the start of January 2015 to the end of December 2016. Data on costs for the economic analysis will be obtained from logistics supply, accounting and pharmacy records, and from time estimates obtained through observation and discussions with staff (see below for more details).

### 3.4.4 Cohort data management

Paper data are collected on a daily basis by existing MSF data clerks and any abnormal or missing values are discussed with the nurse or doctor and both paper and electronic data updated accordingly. Single data entry is performed by a trained data entry operator using a password-protected Excel software database developed for the programme. The local MSF epidemiologist will analyse the routine service data for the cohort study and will ensure the quality of data collection and entry through weekly checks. The data is also emailed to the MSF-OCA NCD advisor on a monthly basis for further quality checks.

The routine cohort data are held on password protected databases and PCs in a secure location. Data used for the cohort analysis will be extracted from the database and anonymised, with removal of unique identifiers other than the MSF identification number. Data on costs for the economic analysis will be held on a secure Excel file.

### 3.4.5 Cohort data analysis

Cohort data from both clinics will be aggregated and will be analysed using RStudio v1.0.136 (RStudio, Boston, MA 02210, USA). Descriptive statistics will be used to describe the patient cohort, explore clinical outcomes and analyse trends in outcome measures from baseline. To attempt to account for programmatic changes that occurred since the intervention began, comparison will be made between patients who entered the programme during different periods. Analysis will include proportions and means, presented with 95% confidence intervals (95%CI). Differences in proportions will be measured using Pearson χ2 test while differences in means will be measured using two-sample t-tests, presented with p-values. Clinical outcomes will be compared using multiple linear regression to explore the effect on key clinical outcomes of age, gender, origin (Syrian or Jordanian), economic status, mobility, type and number of morbidities (including relevant, identified mental health co-morbidity), and number of medications/pill burden.

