This evaluation, including use of routine service data, will take place in the two vertical, primary care based MSF-supported clinics providing NCD care in Irbid city centre. The first clinic was opened in December 2014 within an MoH primary care facility in Ibn-Sena. The clinic is located on the first floor, accessed by stairs only. The second clinic opened in April 2015, alongside a private organization, Arab Medical Relief (AMR), in their facility at Ibn-Rushd. This is located in the basement of a major civic building, also accessed by stairs only. Both clinics may be reached by public transport. Each contains a reception desk, central waiting area, triage room, individual consultation rooms, a larger room for group education sessions and a pharmacy. Ibn-Sena also has a treatment room where diabetic foot care is carried out.

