### 3.4.1 Cohort study area and study population

The study location will be the two MSF-OCA supported clinics in Irbid city, northern Jordan. The first clinic was opened in December 2014 within an MoH primary care facility in Ibn-Sena and the second, opened in April 2015, works alongside a private organization, Arab Medical Relief (AMR), in their facility at Ibn-Rushd.

To date (November 2016), 4672 NCD-related patients (aged 1 to 94 years) have been registered in the two clinics, since patient registration was introduced in December 2014. Inclusion criteria are (1) Socio-demographic [Syrian refugee, refugee from another origin or vulnerable Jordanian (defined as patients who were identified as vulnerable according to the Ministry of Social Development National Aid Fund list) and (2) Medical [confirmed CVD (including angina pectoris, myocardial infarction, ischaemic stroke, peripheral vascular disease), CVD risk factors (HTN), COPD, Asthma and/or DM Type I or II]. Patients must fulfil both criteria. All NCD patients aged six years and older with at least two recorded visits (to enable evaluation of outcomes) will be included in the study cohort. This includes any new patients presenting with a new or existing diagnosis of a target NCD.

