### 3.4.6 Clinical audit

A paper-based checklist (Annexe 2d) will be used by a trained clinical staff member(s) to evaluate a sample of two hundred patient files with ten per cent of the sample cross-checked by the medical supervisor. A randomly selected sample of files of patients enrolled in the programme for over 12 months will be used. In addition, 65 files (based on a precision of 10%) from amongst the patients with asthma will be randomly selected, since the active cohort contains fewer than 300 patients diagnosed with asthma. The data will be anonymised, entered by a trained data entry operator into a password-protected Excel software database, analysed using proportions measured with Pearson’s χ2 test and reported with 95% confidence intervals.

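### The entry-period comparison pools two clinics that opened at different times, with no clinic term or breakdown, so a shift in clinic mix could be read as a programme trend

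*Protocol*

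**What the plan says.** Protocol section 3.4.5 fixes three things.

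- **Pooling:** "Cohort data from both clinics will be aggregated".
- **Handling of programme change:** "comparison will be made between patients who entered the programme during different periods". The tests are unadjusted: "Differences in proportions will be measured using Pearson χ2 test while differences in means will be measured using two-sample t-tests".
- **Regression factors:** "age, gender, origin (Syrian or Jordanian), economic status, mobility, type and number of morbidities", together with number of medications or pill burden. Clinic is not among them.

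Neither sections 3.4.1 to 3.4.6 nor Table 2 provides for cohort or audit results by clinic, and the limitations in section 6 do not mention clinic differences.

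The protocol describes two distinct settings. Section 3.1 says "The first clinic was opened in December 2014 within an MoH primary care facility in Ibn-Sena", and section 3.4.1 adds that "the second, opened in April 2015, works alongside a private organization, Arab Medical Relief (AMR), in their facility at Ibn-Rushd". Section 3.1 also notes that "Ibn-Sena also has a treatment room where diabetic foot care is carried out" and lists no such room for Ibn-Rushd. Under section 3.4.3, cohort entry runs from the start of January 2015 to the end of December 2016.

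For the audit, section 3.4.6 says "A randomly selected sample of files of patients enrolled in the programme for over 12 months will be used". The sample checklist in Annex 2e shows no place for clinic.

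**The concern.** The entry-period comparison is the only stated device for taking account of how the programme changed. It is meaningful only if patients entering in different periods are otherwise comparable. Clinic breaks that condition by construction, because one clinic did not exist for the first three months of the entry window. If the clinics differ in case mix, staffing or level of control, that difference enters the contrast between periods even when neither clinic changed at all.

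The evaluation is meant to say how the model performed as it evolved and to inform its use elsewhere. A change in where patients enrolled, read as a change in how well the programme worked, would mislead on both. A single pooled figure also gives no means of seeing whether the two host settings performed alike.

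**Working it through.** The protocol states no sample size or error rate for this comparison, so there is no figure to reproduce. The check has a structural step and two illustrations. All clinic-level rates and mixes below are assumptions.

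**1. Overlap of clinic and period.** Entry starts in January 2015 (section 3.4.3) and Ibn-Rushd opened in April 2015 (sections 3.1 and 3.4.1). Entrants in January, February and March 2015 are therefore 100% Ibn-Sena. This follows from the dates alone.

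**2. Size of the artefact.** With no true change over time,

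spurious period difference = (Ibn-Rushd share in later period − Ibn-Rushd share in first period) × (between-clinic difference).

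Assume 70% at target in Ibn-Sena, 60% in Ibn-Rushd, and half of entrants at each clinic once both are open. Later entrants then show 0.5 × 70% + 0.5 × 60% = 65%.

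- *First period January to March 2015:* the Ibn-Rushd share is 0, so the rate is 70%. Difference: (0.5 − 0) × 10 = 5 points.
- *First period January to July 2015*, ending before the August 2015 additions described in section 1.1.5, with even monthly entry: Ibn-Sena has (3 + 0.5 × 4)/7 = 5/7 = 71% of entrants. The rate is 5/7 × 70% + 2/7 × 60% = 67.1%. Difference: 67.1 − 65 = 2.1 points.

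If Ibn-Rushd were the better clinic, the sign would reverse.

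**3. How often an unadjusted test would flag it.** Take 3500 patients (section 1.1.1 says over 3500 enrolled). The window has 24 months less the six-month closure to new patients (section 1.1.4), leaving 18 open months. With even entry, 3/18 × 3500 = 583 enter in January to March 2015 and 2917 later. Assume 60% at target in Ibn-Sena and no true change. The probability of rejection at two-sided 5% is then:

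| Between-clinic difference | Later share at Ibn-Rushd | Spurious difference | Rejection probability |
|---|---|---|---|
| 5 points | 30% | 1.5 points | 9.8% |
| 5 points | 60% | 3 points | 26.5% |
| 10 points | 30% | 3 points | 26.5% |
| 10 points | 60% | 6 points | 76.0% |

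If the first period instead holds 10% or 25% of patients, all still from Ibn-Sena, the range over the same settings is 7.7% to 87.4%. Every value exceeds the nominal 5%. This table uses the first period with complete overlap. A longer first period that includes Ibn-Rushd entrants shrinks the spurious difference, as in step 2.

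**The case against.** The strongest defence is that the unit of evaluation is the programme. Both sites follow one MSF model with common guidelines, so a pooled figure answers the question in section 3.4. Pooling also does not forbid a later breakdown, and detailed tables are often left to an analysis plan. This stands for the overall descriptive figures. It does not rescue the period comparison, because the protocol itself fixes the pooling, the unadjusted tests and a factor list without clinic.

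Several stronger readings are tempting but unsupported:

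- *That a 5-point false decline is to be expected.* The protocol sets no cut at April 2015. Complete overlap covers only three months, and the documents report no outcome difference between the clinics.
- *That leaving clinic out of the regression itself creates a false trend.* As listed, that model has no entry-period term. There the omission only leaves a possible source of variation or confounding unexamined.
- *That foot checks must be worse at Ibn-Rushd.* The protocol mentions a treatment room at one site. It does not say that checks cannot be done in the other site's consultation rooms.
- *That the audit sample is defective.* A simple random sample of 200 files represents the clinics roughly in proportion, so stratifying adds little. Annex 2e is a sample form with no header fields at all, so the missing clinic field is weak evidence of a deliberate choice.

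Two further points stand. Within-patient trends from baseline are less exposed to clinic mix than comparisons between entry cohorts. Differences between the settings are also partly explored by observation and interviews (section 3.7).

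**Conclusion.** The concern holds for the entry-period comparison. The opening dates tie clinic mix to entry period, and the stated analysis has nothing to separate them, so a stable between-clinic difference could be reported as programme change. Whether such a difference exists, and in which direction, cannot be told from the documents. Under the assumed 70% and 60% rates and an even later mix, the artefact runs from about 2 to 5 points according to where the first period ends. It would be zero if the clinics perform alike. The absence of results by clinic is a lesser point, and the audit needs only to record clinic.

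**What to change.** In section 3.4.5:

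- make the entry-period comparison within clinic, or adjust it for clinic;
- state that January to March 2015 entrants have no Ibn-Rushd counterpart, so any contrast involving those months rests on Ibn-Sena alone or on an assumption that the period effect is the same in both clinics;
- add clinic as a fixed factor in the regressions (two clinics are too few for a random effect);
- report the principal clinical and quality outcomes by clinic beside the pooled figure.

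In Annex 2e, record clinic so that fidelity items, including foot checks, can be shown descriptively by clinic. The audit sampling can stay as it is.

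**Cost.** Some wording, one model term and one form field. Section 1.1.6 does not name clinic among the recorded variables, so it may have to be derived from where the file is held (section 1.1.2 says files are stored at each clinic). A rule is needed for home-visit patients, of whom 150 have been enrolled. Per-clinic audit figures will be imprecise. If 60% of the 200 files are diabetic (assumed), the 95% half-width at 80%, 1.96 × √(0.8 × 0.2/n), is about 7 points for all 120, 10 points for 60 in one clinic, and 14 points if a clinic supplies only 30. They should therefore be presented descriptively, without a test between clinics.
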